# A cluster randomised trial to evaluate the effectiveness of household alcohol-based hand rub for the prevention of sepsis, diarrhoea, and pneumonia in Ugandan infants (the BabyGel trial): a study protocol

**DOI:** 10.1186/s13063-023-07312-1

**Published:** 2023-04-17

**Keywords:** Sepsis, Alcohol-based hand rub, Newborn, Neonatal, Uganda, Infections

## Abstract

**Background:**

Infections are one of the leading causes of death in the neonatal period. This trial aims to evaluate if the provision of alcohol-based hand rub (ABHR) to pregnant women for postnatal household use prevents severe infections (including sepsis, diarrhoea, pneumonia, or death) among infants during the first three postnatal months.

**Methods:**

Through a cluster-randomised trial in eastern Uganda, 72 clusters are randomised in a 2-arm design with rural villages as units of randomisation. We estimate to include a total of 5932 pregnant women at 34 weeks of gestation. All women and infants in the study are receiving standard antenatal and postnatal care. Women in the intervention group additionally receive six litres of ABHR and training on its use. Research midwives conduct follow-up visits at participants’ homes on days 1, 7, 28, 42, and 90 after birth and telephone calls on days 14, 48, and 60 to assess the mother and infant for study outcomes. Primary analyses will be by intention to treat.

**Discussion:**

This study will provide evidence on the effectiveness of a locally available and low-cost intervention in preventing neonatal sepsis and early infant infections. If ABHR is found effective, it could be implemented by adding it to birthing kits.

**Trial registration:**

Pan African Clinical Trial Registry, PACTR202004705649428. Registered 1 April 2020, https://pactr.samrc.ac.za/.

**Supplementary Information:**

The online version contains supplementary material available at 10.1186/s13063-023-07312-1.

## Background

Globally, an estimated 5 million children younger than five years of age die annually [1]. The leading causes of global under-5 deaths are neonatal morbidity (37.3%), followed by lower respiratory tract infections such as pneumonia (13.3%) and diarrhoeal diseases (9.9%) [1]. While mortality after the first 28 days of life in Uganda has significantly reduced in the last two decades, reduction in neonatal mortality has been slow with an 18% reduction (from 33 to 27 deaths per 1000 live births) [2]. Infections are one of the leading causes of death in this neonatal period [3]; the common neonatal clinical conditions of sepsis, meningitis, and pneumonia account for approximately one third of all neonatal deaths in sub-Saharan Africa [4]. Reducing infant infections is therefore a prerequisite for Uganda to reduce the neonatal and under-5 mortality and therewith achieve the Sustainable Development Goal 3 (SDG target 3.2: ‘reduce neonatal mortality to less than 12 deaths per 1000 live births and under-5 mortality to at least as low as 25 per 1000 live births’) [5, 6].

Poor sanitation and hygiene amongst parents and other carers as well as a lack of proper hand-washing facilities contributes to the high burden of infections [7, 8]. In the most recent Ugandan National Household Survey, only 19% of the households used improved toilet facilities, and only 59% had a hand washing facility [7]. Furthermore, pilot work from the BabyGel scoping survey in Mbale district showed that approximately 53% of mothers do not wash their hands regularly and 47% of mothers only wash their hands when they are heavily soiled. Hand hygiene has been a high priority for the World Health Organization (WHO), emphasised in the ‘Seconds save lives: clean your hands’ global campaign since 2009 [9]. Unfortunately, in most low-income countries (LIC), compliance to hand washing even among health workers in critical medical situations is only about 10% [10]. Interventions to promote hand hygiene in LICs are needed.

The WHO campaign states that reliable uninterrupted provision of good-quality ABHR would improve hand hygiene [9]. However, there is little high quality evidence to support this advice, especially for community settings. A quasi-experimental study at Mbale Regional Referral Hospital noted that provision of ABHR in hospital wards coupled with training greatly improved hand hygiene [11]. In contrast to hospital settings, the provision of latrines, hand-washing facilities and hygiene education to communities in Zimbabwe had no effect on rates of infant infection or their gut microbiome despite the facilities being well used [12]. An intervention such as ABHR use by the caregiver that is closer to the infant may therefore be needed to break the faecal-oral transmission pathway. In this study, we aim to determine whether the community based provision of ABHR with hygiene training to pregnant women for postnatal household use is effective for the prevention of severe illness or death during the first 3 months of life.

### Study objectives

#### Primary objective

To evaluate the effect of ABHR use by carers on severe illness or death in infants in the first 3 months of life.

#### Secondary objectives

To evaluate the effect of ABHR use by carers in infants in the first 3 months of life:On rates of diarrhoeaOn rates of respiratory tract infectionsOn rates of omphalitisOn rates of other infectionsOn linear and ponderal growth

In addition:To estimate the cost of providing ABHR and assess the cost-effectiveness of providing the ABHR use versus normal practiceTo explore the effect of ABHR provision on maternal behaviourTo evaluate the effect of ABHR use on rates of maternal sepsis

#### Exploratory objectives

To explore the relationship between health inequalities and rates of maternal and infant morbidityTo explore current hand hygiene practices and options of improving practice in rural Ugandan villagesTo explore the mechanisms of action (mediators and moderators) of caregiver ABHR training on prevention of severe illness or death during the first 3 months of life

## Methods

### Study design

This study is a phase 3 open-label, 2-arm, stratified cluster-randomised controlled trial. ABHR is not classified as a drug in Uganda and this is therefore not a Clinical Trial of an Investigational Medicinal Product.

### Study setting

The trial is being conducted in Mbale and Budaka Districts in Eastern Uganda, located at the foot of Mt Elgon and approximately 230 km east of the capital Kampala.

#### Hand washing practices

In Uganda, hand washing usually takes place with the midday meal when hands are washed with water before and after eating. In addition, people often wipe their hands on a cloth throughout the day. As a consequence, their hands are often free of particulate matter, allowing for alcohol-based hand rub to be effective.

#### The BabyGel pilot trial

A pilot trial was conducted on the provision of ABHR to postpartum mothers to prevent neonatal infective morbidity [13]. The average gel use over 3 months was 2.5 litres (range 1.1–4.1). There was also evidence of a behavioural effect of having the ABHR, with an increase in care-seeking behaviour in the treatment clusters [14]. Participant interviews and focus groups showed high knowledge, acceptability and compliance with the study intervention.

### Study population

Eligible participants are women who are over 34 weeks pregnant (estimated by menstrual or ultrasound scan dates or physical observation) and residing in the included 72 clusters.

#### Inclusion criteria

Participant is willing and able to give informed consent for participation,Female, aged 18 years or above, or those under 18 so long as they are emancipated,At least 34 weeks pregnant,Living in one of the clusters in Mbale or Budaka Districts, defined within this study protocol, and planning to be live there for birth and the first 3 postnatal months.

#### Exclusion criteria

Women who have previously participated in the BabyGel study and present with a further pregnancy

### Intervention

The Ugandan government encourages the public to use ABHR. ABHR has been declared a safe public health item, and the BabyGel pilot study confirmed safety, tolerability, and acceptability of the ABHR [13, 15].

#### Comparator arm

All participants receive standard antenatal care including health information regarding hand hygiene with soap and water, and a Maama birth kit (Picture 1). Following recent national recommendations, all women also receive chlorhexidine for cord care [16]. All women receive an initial visit from the research midwives at home after 34 weeks in addition to standard antenatal care at the local hospital or health centre.

#### Intervention arm

Women in the intervention arm receive all the comparator arm interventions as above. In addition, they receive a total of six litres of ABHR: a full 1-litre dispenser for use at home and an empty 60 ml-bottle for use outside of the house) and a 5-litre container for refill (Picture 2).

When the ABHR is delivered, each household obtains training on the correct use of ABHR in late pregnancy and postnatal. This is repeated at fortnightly meetings, face-to-face, or by telephone, until the participant gives birth (Table 1). During the scheduled visits, the trainer measures the amount of remaining ABHR in order to monitor usage and counsels the participant if ABHR is being underused or overused. Implementing provision of ABHR will not require alteration to usual care pathways and these will continue for both trial arms. We will discontinue the ABHR if the participant develops a reaction to the product or requests to opt out.

**Table 1 Tab1:** Participant’s timeline with study procedures conducted by research midwife (RM) for recruitment and follow-up and by the ABHR trainer

	**Study period**													
	**Enrolment**	**Post-enrolment**												**Exit**
**Timepoint**	***Week 34***^a^	***Week 34***^a^	***Week 36***^a^	***Week 38***^a,b^	***Week 40***^a,b^	***48 hours***	***Week 1***	***Week 2***^b^	***Week 4***	***Week 6***	***Week 8***^b^	***Week 10***^b^	***Week 12***	***Week 12***
**Enrolment:**														
**Eligibility screen**	X													
**Informed consent**	X													
**Interventions:**														
***Training on ABHR use***		X	X	X	X	X								
***Assessment of ABHR use***			X	X	X	X								X
**Assessments:**														
***Baseline data collection***	X													
***Clinical, AE and SAE assessment, anthropometry***		X	X	X	X	X	X	X	X	X	X	X	X	
***Outcome assessment***						X	X	X	X	X	X	X	X	

^a^If still pregnant

^b^Telephone visit

A double-sided poster (Appendices 1 and 2) supplements the training, summarising the instructions in both a written and visual format, with one side specifying the correct antenatal and one the correct postnatal use of ABHR. The key message is that everyone should use ABHR “before touching the baby” (Appendix 3).

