### Identification, recruitment, and study procedures

The study processes were initially piloted in 10 villages [13] and refined, resulting in this final procedure. The village health team (VHT) member identifies potential participants and inquires whether they are interested in being enrolled in the study. Women may also be identified when presenting at antenatal clinics in hub facilities. The VHT notifies the research midwife about the potential participant. The research midwife visits the home and spends time with the woman explaining the study, what is involved, how long the woman and her baby are involved in the study and whether she is willing to give informed consent to participate. Each woman is told that once she has given her consent, she is free to withdraw from the study at any point and that the care and treatment of herself and her baby will not be affected. Should a woman withdraw from the study, the research team gently question her to attempt to ascertain the reason for her withdrawal from the study. The same is done for women who decline to enrol. No pressure is exerted should the woman be resistant to giving a reason, but feedback obtained from this interaction provides valuable feedback to the research team for approaching other women in the study.

Those in the intervention arm are given their supply of ABHR and trained fortnightly in its use by the ABHR trainer in a series of antenatal visits and reminder calls. Those in the control arm receive only a single recruitment visit antenatally in addition to standard antenatal care.

A VHT member (or the woman herself) is encouraged to inform the BabyGel midwives or hotline (calls are free of charge) when she has given birth and a research midwife visits within 48 h either at the participant’s home or at a health facility if the participant is still admitted. The same research midwife performs regular telephone calls and personal follow-up visits up to 12 weeks (trial completion).

The women are screened and recruited into the study at 34 weeks’ gestation. Gestational age is measured using an application on the midwives’ tablet or the obstetric ultrasound report if available or physical inspection. The women and their babies are followed for 3 months post-delivery. Therefore, participating women completing the follow-up period will be active in the study for approximately 20 weeks (± 2 weeks to account for inaccurate gestational age estimations).

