### Safety reporting

Safety of the women and babies participating in this study is paramount. Although this is not a clinical trial of an investigational medicinal product, safety data on both the women and the babies (including adverse events (AEs) and serious adverse events (SAEs) are collected carefully and reported to the sponsor, local IRB, and the Independent Safety and Data Monitoring Committee (ISDMC). The key participants in this study are the neonates, and adverse events that could be influenced by the trial interventions are outcomes for the study. Data on these events are recorded on the electronic Case Report Forms (CRFs).

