Missing baseline covariates will be imputed using simple imputation methods in the covariate-adjusted analysis based on the covariate distributions. For a continuous variable, missing values will be imputed from random values from a normal distribution with mean and SD calculated from the available sample. For a categorical variable, missing values will be imputed from random values from a uniform distribution with probabilities P1, P2, …, and Pk from the sample. For a count data, missing values will be imputed from random values from a Poisson distribution with λ from the sample. Seed for the imputation is set as 128.

Due to the nature of the study, no stopping rules have been set. Any decision to stop the study will be based on a combination of rates of adverse events, recruitment rate, interim data analysis, and the results of other recently published studies. The final decision to stop the study would be made by the trial steering committee.

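### Table 1 marks adverse-event assessments at weeks 36, 38 and 40 for all women, but the text gives controls only one antenatal study visit; reconcile them, or antenatal adverse-event rates are not fully comparable

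*Protocol article*

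**What the plan says.** Table 1 is a single participant timeline for both arms, covering the work of both the research midwife and the trainer. Its row "Clinical, AE and SAE assessment, anthropometry" is marked at weeks 34, 36, 38 and 40 of pregnancy and then at 48 hours and weeks 1, 2, 4, 6, 8, 10 and 12 after birth. Footnotes limit the four antenatal columns to women "If still pregnant" and label weeks 38 and 40 "Telephone visit". The separate outcome-assessment row has only the eight postnatal marks.

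The section on identification, recruitment and study procedures states: "Those in the control arm receive only a single recruitment visit antenatally in addition to standard antenatal care". The comparator-arm section agrees, describing one initial midwife visit at home after 34 weeks. The Abstract places all midwife follow-up visits and calls after birth.

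For the intervention arm, the recruitment section says women are "trained fortnightly in its use by the ABHR trainer in a series of antenatal visits and reminder calls". The intervention-arm section says of the training: "This is repeated at fortnightly meetings, face-to-face, or by telephone, until the participant gives birth".

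Under Safety reporting, "safety data on both the women and the babies (including adverse events (AEs) and serious adverse events (SAEs) are collected carefully". The Statistical analysis plan section sets no stopping rules but says: "Any decision to stop the study will be based on a combination of rates of adverse events, recruitment rate, interim data analysis", together with the results of other recent studies.

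**The concern.** Read literally, Table 1 requires three antenatal adverse-event assessments after enrolment for every woman still pregnant, while the text leaves controls with no scheduled study contact at which to make them. One of the two is wrong or incomplete.

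If the text is right, events between enrolment and birth are actively sought in one arm. In the other they reach the record only through standard antenatal care, the woman's own report, the village health team, or recall at the first postnatal visit. Because adverse events are collected on women as well as babies, antenatal maternal events enter the safety data. A between-arm rate that includes the antenatal period would then tend to be higher in the intervention arm through ascertainment alone. The same asymmetry could mask a true excess in controls. Adverse-event rates are a named input to any decision to stop, and with no formal rule there is no threshold or definition to guard against such an artefact.

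**Working it through.** The plan states no figure on this point, so there is none to reproduce. The check is a count of contacts followed by an illustration of size.

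**Contacts, from Table 1 and the recruitment section**

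- Adverse-event row: 4 antenatal + 8 postnatal = 12 marks.
- Controls, if the single antenatal visit is the week-34 one: 1 + 8 = 9.
- Weeks 36, 38 and 40 count only while the woman is still pregnant. For enrolment at week 34:

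| Birth at week | Extra intervention-arm contacts | Intervention v control |
|---|---|---|
| 36 or earlier | 0 | 9 v 9 |
| 38 | 1 (week 36) | 10 v 9 |
| 40 | 2 (weeks 36, 38) | 11 v 9 |
| 42 | 3 (weeks 36, 38, 40) | 12 v 9 |

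So 12 against 9 (ratio 12/9 = 1.33) is the maximum, and birth at week 40 gives 11/9 = 1.22. Eligibility is at least 34 weeks, so a woman enrolled later has fewer extra contacts.

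**Apparent rate ratio when the true rates are equal**

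Assumptions, none of them given in the article: enrolment at week 34; a constant event rate per person; mother and baby each followed for 12 weeks after birth; the fetus not counted separately; complete capture in the intervention arm and, after birth, in both arms; a fraction c of antenatal events captured in controls.

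- Antenatal time for birth at week 40: 40 − 34 = 6 woman-weeks.
- Postnatal time: 12 + 12 = 24 person-weeks.
- Antenatal share: s = 6 / (6 + 24) = 0.20.
- Apparent ratio, intervention to control: R = 1 / (1 − s + s × c).

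| c in controls | Calculation | R |
|---|---|---|
| 80% | 1 / (0.80 + 0.16) | 1.04 |
| 50% | 1 / (0.80 + 0.10) | 1.11 |
| 0% | 1 / 0.80 | 1.25 |

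Varying the week of birth:

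- Week 38: s = 4/28 = 0.143, giving R = 1.03, 1.08 and 1.17.
- Week 42: s = 8/32 = 0.25, giving R = 1.05, 1.14 and 1.33.

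**What is not touched**

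The Abstract lists five postnatal visits and three calls, which agrees in number with the eight postnatal marks. These apply to both arms, so from birth onward the schedule is 8 v 8.

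**The case against.** The strongest reply is that this is an ambiguity in a condensed table. Table 1 already contains rows that can apply only to the intervention arm, and the adverse-event row bundles anthropometry into columns marked as telephone contacts, so not every element can apply at every mark. If the week 36 to 40 marks are meant for both arms, the recruitment section is merely incomplete and there is no bias. That stands as a reason to state the consequence conditionally. It does not remove the need to reconcile the passages.

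Four stronger readings are tempting, and the document does not support them.

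- A reader might infer that unmasked trainers assess adverse events. No passage says so. Midwives are described as the data collectors, and the trainer's stated tasks are training, measuring remaining hand rub and counselling on its use.
- A reader might infer that the monitoring committee will see a false safety signal that could stop the trial. The article does not say that antenatal and postnatal rates are pooled or compared by arm. Adverse-event rates are one input among several, there is no stopping rule, and the steering committee decides.
- A reader might take 6 antenatal weeks out of 18, a share of one third, which gives ratios of 1.07, 1.20 and 1.50. That fits a rate restricted to mothers. The Safety reporting section counts women and babies.
- A reader might assume that controls' antenatal events are lost entirely. Controls have standard antenatal care, the village health team, a free hotline and a 48-hour visit with its own adverse-event mark. Zero capture is therefore an outer bound. The article does not say whether the 48-hour assessment reaches back to enrolment.

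It is also fair to say that extra product-safety contact in the arm holding the product is ordinary practice. That is a reason to keep those data but report them apart from between-arm rates.

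**Conclusion.** The point holds in a limited form. Table 1 and the account of control-arm contacts disagree about weeks 36, 38 and 40, and this needs correcting whichever is right. If the single-visit statement is right, ascertainment of antenatal, mainly maternal, adverse events differs by arm, and rates that include that period are not fully comparable. The likely distortion is modest: about 1.04 to 1.11 for birth at week 40 with 80% to 50% capture in controls, and 1.25 at the bound of no capture. These figures rest on an assumed constant rate per person, an assumed gestation at birth and assumed capture fractions. Infant events and the primary outcome follow the same postnatal schedule in both arms and are not affected.

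**What to change.** 1. Annotate Table 1 by arm, and by who makes each contact, and reconcile weeks 36, 38 and 40 with the statement of a single antenatal study visit for controls.
2. Base any between-arm comparison of adverse or serious adverse event rates on the eight postnatal contacts common to both arms.
3. At the existing 48-hour visit, ask women in both arms the same questions about events between enrolment and birth, and use only those answers for an antenatal comparison.
4. Report events found only at intervention-arm antenatal contacts separately, as product safety in that arm and not as a between-arm rate.

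The cost is a table edit, one block of questions at a visit that already takes place, and a changed layout for the safety tables. Recall at 48 hours will miss some antenatal events, but in both arms alike. Recruitment was still under way when the article appeared, so the new questions would cover only births after their introduction; the restriction to postnatal contacts can be applied to all participants.

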#### Trial organisation

For ease of study implementation, the study area is divided into three geographical areas each consisting of a minimum of 24 clusters, each with a study management site (‘hub’) hosted at the largest government run health facility in the area, in Busiu Health Centre (HC) IV, Budaka HC IV, and Kolonyi HC III, respectively. Each hub has a study doctor, village health team members and supervisors, a data manager, at least 7 research midwives to collect data, and 3 staff to train mothers in ABHR use. A cluster is eligible for inclusion in the study if the 1–4 village(s) constituting it have more than 600 inhabitants collectively and if it is not directly neighbouring another cluster (to prevent communication and intervention contamination). The aim is an average cluster size of 850 inhabitants. We surveyed each participating cluster prior to the initiation of the study to determine the population of children under the age of 2 years as a proxy for that cluster’s birth rate. In total, we expect to recruit 5932 pregnant women. Consent was obtained from the leaders of all included villages to approach and recruit mothers potentially eligible for inclusion in the study.

